**Figure 2 figure2:**
[figure not shown]
Screenshots of Visualize portion of study app showing data collected from Fitbit and variables computed from mathematical modeling. HR: heart rate.

To accompany these measures of adherence and engagement, we will also use other responses on the engagement survey to further examine reasons why an individual might monitor their symptoms with either a mobile phone or an activity tracker. Since responses are in the form of multiple-choice options, we will report number and proportion of participants in the entire group and in each arm, who choose each option.

#### Secondary Outcome Measures

Secondary outcome measures evaluate whether symptoms improve in the study: change from baseline in severity of manic symptoms, as measured with the YMRS; and change from baseline in severity of depressive symptoms, as measured with the 17-item SIGHD. We hypothesize that by tracking symptoms throughout the study, individuals with BP improve their symptoms. Establishing validity of this hypothesis will serve to reinforce the importance of monitoring symptoms in BP as a target in therapy.

#### Exploratory Aims

Along with evaluating primary and secondary measures above, the data collected from this study provides opportunities to examine other questions. For one, we want to establish validity of our mobile-based 6-item survey for tracking BP, by determining to what extent the 6 symptoms can explain total scores on the weekly interview-based YMRS and SIGHD total scores as was demonstrated in our preliminary analysis. Additionally, we want to examine other strategies for increasing engagement in monitoring BP symptoms. To that end, we will examine responses on our engagement survey about providing charts and graphs of user data over time, top 3 uses of technology for monitoring symptoms, top 3 barriers of preventing technology from being used to monitor symptoms, and top 3 symptoms or patterns to monitor. Finally, we want to evaluate mathematical models for personalizing phenotypes of BP based on *daily* patterns of mood in BP [11].

#### Statistical Tests

For the first two primary outcome measures, we will test whether proportions are statistically different from 0.5 using a binomial test. These tests answer whether users prefer and adhere to monitoring symptoms using apps over activity trackers. For the second two primary outcome measures, we will test whether adherence rates are statistically different between arms using a 2-sample Student *t*-test if variances can be assumed to be equal, otherwise a Welch *t* test will be used. These tests answer whether users better adhere to monitoring symptoms with apps and activity trackers when reviewing collected information weekly with an interviewer. For the secondary outcome measures, we will test whether individuals experience a statistically significant increase in YMRS and SIGHD scores from baseline over the course of the 6-week study using McNemar test, which compares the number of individuals whose survey scores increased versus those whose survey scores decreased. For all statistical tests, significance will be considered a *P* value less than .05.

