## Methods

### Recruitment

In total, 50 individuals with BP will be recruited from the Prechter Longitudinal Study of Bipolar Disorder [30] to participate in a 6-week, 2-arm randomized controlled trial. This 6-week study has been approved by institutional review boards at the University of Michigan (HUM126732) and University of Wisconsin (2017-1322). Participants in the Prechter study have already completed a Diagnostic Interview for Genetic Studies about their health and mental illness history. We will access the diagnostic information and other data from the longitudinal study so as not to repeat the interview process. Individuals will be included if they (1) have agreed to be contacted for future research, (2) have a mobile phone, and (3) have a diagnosis of BP. Participation is open to men and women; to adults (aged 18 years or older); and to all ethnic and racial groups. To select participants from the larger trial, a data manager pulled a query of participants with diagnoses of either BP I, BP II, or BP NOS (not otherwise specified) and who have authorized contact for future studies. Participants are ordered by authorization date, with most recent dates at the top of the list and recruitment emails are sent in this order. Individuals who express interest and have a mobile phone are then consented.

The study aims to be balanced by age and gender and to achieve adequate representation of minorities as reflected by the diversity of Washtenaw and surrounding Counties of Michigan, in which most participants live. All participants will be consented, which involves a discussion over the phone, followed by submission of consent electronically through the data capture software REDCap (see Multimedia Appendix 1 for Informed Consent document). Sample size and observation length are based on 3 auxiliary studies of the Prechter study finding significant associations between variables and significant differences in measurements between two groups, assuming about 10% to 20% attrition.

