### Randomization

Each participant is randomly assigned to one of the two arms (Arm NR=No Review or Arm R=Review), stratified by age and gender. Each participant has a 50-50 chance of being assigned to Arm R. Following weekly mood assessments, Arm R reviews information collected over the week with an interviewer, whereas Arm NR does not discuss this information. Subjects and interviewers will necessarily be unblinded. A randomized list of assignments to one of the two arms was generated for 4 groups: women <40 years of age (N=13), women ≥40 years of age (N=13), men <40 years of age (N=12), and men ≥40 years of age (N=12). The randomized list was generated using a random number generator in Matlab (Mathworks; Natick, MA) and a block design, which involves generating random assignments in smaller blocks of participants and then randomly permuting the order of blocks. Because the 2 women groups had an odd number, these blocks were each unbalanced but together ensured equal participants in each arm; the arm that was over-represented in each group was chosen uniformly at random. Additional randomized blocks were appended to the randomization list in case of dropout. Although unblinded, arm assignments are not revealed until individuals are recruited and consented to avoid selection bias.

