#### Log Your Mood

Lorevimo’s main function is to log manic and depressive symptoms and medication adherence (Figure 1). Users can log symptoms, once in the morning and once in the evening, to capture diurnal patterns in mood characteristic of BP. Morning and evening is defined based on a participant’s self-reported wake and bed times on weekdays and weekends: respectively, the 6-hour window spanning 2 hours before to 4 hours after their typical wake time and the 6-hour window spanning 4 hours before to 2 hours after their typical bed time. Typical bedtimes or wake times are entered by the user when they first log into the app and can be changed anytime under Settings in the app. Automatic reminders via push notifications are sent at 2-hour intervals for individuals who are yet to log symptoms, are within the appropriate window, and not too close to their typical bedtime or wake time.

**Table 1 table1:** Summary of study participation and information collected on each participant.

Interaction	Instruments	Study days
Entrance phone interview	YMRS^a^, SIGHD^b^, RAND SF-36^c^	0
App self-report	3 items from YMRS, 3 items from SIGHD, medication adherence (only in the morning)	0-42, twice
Offline computed variables	Computed variables: circadian phase and amplitude and cumulative sleep debt	0-42
Activity tracker	Activity, sleep, heart rate	0-42
Weekly phone interview	Both arms: YMRS, SIGHD. Arm R only: review of collected data from app and activity tracker	7, 14, 21, 28, 35
Exit phone interview	YMRS, SIGHD, RAND SF-36, Engagement survey	42

^a^YMRS: Young Mania Rating Scale.

^b^SIGHD: Structured Interview Guide for the Hamilton Rating Scale of Depression.

^c^SF-36: 36-Item Short Form Health Survey.

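### The two between-arm primary comparisons use an unadjusted t-test although randomisation is stratified by age and gender; the test is valid but gives up power if the strata predict adherence

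*Protocol article*

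**What the plan says.** The Recruitment section sets the size: "In total, 50 individuals with BP will be recruited", with 10% to 20% attrition assumed. It gives no effect size, SD or power.

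The Randomization section says that assignment is "stratified by age and gender", using blocks within four groups: women under 40 (13), women 40 or over (13), men under 40 (12) and men 40 or over (12). Allocation is equal: "Each participant has a 50-50 chance of being assigned to Arm R". Participants and interviewers are unblinded, and "arm assignments are not revealed until individuals are recruited and consented".

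The Statistical Tests section covers the last two of the four primary outcomes, which the Primary Outcome Measures section numbers second and third: "we will test whether adherence rates are statistically different between arms using a 2-sample Student" t-test, with Welch as the alternative when equal variances cannot be assumed. No stratum or other covariate is named. The significance rule is "For all statistical tests, significance will be considered a *P* value less than .05".

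Primary Outcome Measures defines both adherence rates as proportions of study days. Table 1 collects app and tracker data on days 0 to 42. It lists what separates the arms as "Arm R only: review of collected data from app and activity tracker", at the weekly interviews on days 7, 14, 21, 28 and 35. The day-0 interview contains no review.

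**The concern.** Blocking within strata balances age and gender across the arms, so the observed difference between arms varies less than it would under simple randomisation. An unadjusted t-test does not use this: variation between strata stays in its error term and the standard error is too large whenever the strata predict the outcome. The result is a test that rejects too rarely and has less power than the design allows.

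The outcome window is a separate matter. About one week of the six comes before the first review but counts in the adherence rate. If review acts only once it has happened, that week dilutes the difference.

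These are the only two randomised comparisons among the four primary outcomes, and at most 50 people contribute to them. A few power points matter at that size.

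**Working it through.** **No figure to reproduce.** The article gives 50 participants without an effect size, SD or power. The calculations below assume a true difference of 0.8 SD and a two-sided 5% test. The share of variance explained by the strata (R²) is also an assumption, so a range is shown.

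**Reference.** With 25 per arm, the noncentrality is 0.8/√(2/25) = 2.83 on 48 degrees of freedom, which gives power of 79%. A power of 80% needs a difference of 0.81 SD.

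**Strata.** With balance within strata, the true standard error of the difference is about √(1 − R²) times the value that the unadjusted test estimates. A model with arm and four strata uses residual SD √(1 − R²) on 50 − 5 = 45 degrees of freedom. Its noncentrality is 2.83/√(1 − R²):

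- R² = 0: 2.83, power 79%
- R² = 10%: 2.83/0.949 = 2.98, power 83%
- R² = 20%: 2.83/0.894 = 3.16, power 87%

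A simulation with groups of 13, 13, 12 and 12 (40,000 runs per setting) compares the two analyses directly:

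| R² | Type I error, planned test | Power, planned test | Power, with strata |
|---|---|---|---|
| 0% | 5.0% | 79% | 78% |
| 10% | 3.9% | 79% | 83% |
| 20% | 2.8% | 80% | 87% |

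A second simulation with the same group sizes gave type I error of 4.9%, 4.2% and 2.6%, and power of 79% vs 78%, 80% vs 83% and 82% vs 87%. The loss is therefore nil at 0%, 3 to 4 points at 10% and 5 to 7 points at 20%.

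**Outcome window.** Days 0 to 42 are 43 days, of which days 7 to 42 are 36. If review has no effect before day 7 and a constant effect of 0.8 SD afterwards, the all-days mean carries 0.8 × 36/43 = 0.67 SD. With 10% attrition (45 analysed, 22.5 per arm) and the same SD for both windows:

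- all days: 0.67/√(2/22.5) = 2.25, power 59%
- days 7-42: 0.80/√(2/22.5) = 2.68, power 75%

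The five-week mean is slightly more variable than the six-week mean. Allowing for this with weekly correlations of 0.3 to 0.9, and with 25 per arm, gives 64% for six weeks against 77% to 79% for weeks 2 to 6.

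**Days 0-6 as a covariate.** Take 45 analysed, an effect of 0.8 SD and a correlation of 0.5 between the two periods. Adjustment removes 0.5 times any week-1 effect and reduces the SD to √0.75 = 0.866.

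- No effect in week 1: 0.8/0.866 = 0.92 SD, power 86%, against 59% for all days.
- Half the effect in week 1: (0.8 − 0.5 × 0.4)/0.866 = 0.69 SD, power 62%, against 67%.
- Full effect in week 1: (0.8 − 0.5 × 0.8)/0.866 = 0.46 SD, power 33%, against 75%.

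**The case against.** The strongest reply is that nothing here is an error. The unadjusted t-test does not inflate type I error, and nothing in the article says that age or gender predicts adherence. If they do not, adjustment gains nothing. This stands, and it limits the point to efficiency. A reader might infer that the planned test runs below its nominal 5% in any case; the documents do not support that, because it depends on an unknown R².

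A reader might also infer that days 0-6 are a clean pre-intervention baseline and that adjusting for them would raise power from 59% to 86% or more. The documents do not support that either. Participants are unblinded, and the arm is withheld only until consent; nothing says that it is withheld until day 7. Someone who knows that an interviewer will go through the week's data may behave differently from day 0. Averaging over all days is then a legitimate estimate of the effect of being assigned to weekly review, and the covariate would remove part of that effect.

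The Student/Welch choice has no stated criterion, but with near-equal arms the two tests almost coincide, so it is minor.

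Finally, adjustment or a supporting window may appear in the detailed protocol or in an analysis plan. That is possible. But the article itself names the test for these outcomes, so the choice has been made and can be commented on.

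**Conclusion.** The point holds as a matter of efficiency, not validity. The planned test is valid, and it is conservative only to the extent that age and gender predict adherence. At 50 participants and an assumed 0.8 SD, the power loss is about 0, 3 and 6 points when the strata explain 0%, 10% and 20% of the variance, with type I error of about 5%, 4% and 2.6%. Both the effect size and R² are assumptions.

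The outcome window could cost more: about 59% power against 75% at 45 analysed. That holds only if review has no effect before day 7, which the open design leaves uncertain. It justifies a supporting analysis, not a change of primary outcome or a week-1 covariate.

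**What to change.** Replace the Student/Welch t-test for the two between-arm outcomes with a linear model for adherence containing arm and the four age-by-gender strata. Prespecify one method of inference: ordinary t-based inference, or a permutation test within strata. Either removes the Student/Welch choice. An unspecified robust standard error is not a safe substitute at this size. In a simulation with 44 participants, the simplest sandwich estimator with normal critical values gave about 7% type I error. The HC3 version with t critical values gave about 4%, with power of 69% to 73% for R² of 0% to 10%, against 74% for the planned test.

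Keep all study days as the primary outcome window. Add a prespecified supporting analysis of adherence on days 7-42 with the same model. Do not adjust for adherence on days 0-6 unless the arm is in fact undisclosed until the day-7 call.

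The cost is analysis wording and three degrees of freedom (48 to 45), which is under one power point if the strata turn out to be uninformative. No new data are needed.

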**Figure 1 figure1:**
[figure not shown]
Screenshots of study app Lorevimo, which derives its name from the app’s 3 main functions: to log, review, and visualize your mood.

Six symptoms are logged each morning and evening: 3 for mania (increased energy, rapid speech, irritability) and 3 for depression (depressed mood, fidgeting, fatigue). In the morning, users also mark whether they took their medicine on the previous day. We remark that the 6 symptoms capture the various ways in which symptoms manifest in BP, including *anxious* depression (depressed mood+fidgeting); *anehedonic* depression (depressed mood+fatigue); *euphoric* mania (increased energy+rapid speech); *irritable* mania (irritability); and *mixed* states (depressed mood+increased energy). All symptoms are scored on a 0 to 3 scale with 0=absent/normal, 1=mild, 2=moderate, and 3=severe. Ordinal scales were used as opposed to visual analog scales to be consistent with YMRS and SIGHD to clearly identify the absence of symptoms as zero and to ensure individuals can discriminate between choices.

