## Discussion

### Principal Findings

We presented a study on engaging individuals with BP in self-monitoring symptoms with a mobile phone app and activity tracker. Individuals with BP are characterized by extreme shifts in their mood ranging from mania to depression, which often arise quickly and without warning. The WHO recommends that individuals with BP monitor their symptoms [8], and many psychosocial interventions in BP include some form of monitoring symptoms to provide early warnings, raise awareness of symptoms, and provide insight into an individual’s illness [2]. Perhaps most importantly, monitoring of symptoms is a minimum requirement to determine effective adaptive interventions that deliver the *right* psychosocial interventions to the *right* individual at the *right* moment [14]*.* Making it easier to monitor symptoms is the promise of mobile and wearable technology, mirroring a larger trend for chronic diseases such as BP.

Our goal is to ensure that such technology is optimally designed and evidence-based for monitoring symptoms in BP. We thus focus on formally testing 3 engagement strategies: using activity trackers rather than self-reports in a mobile phone app; reviewing collected information weekly; and synthesizing information with charts and graphs. We expect to verify that the individuals with BP prefer and better adhere when using activity trackers over self-reports in a mobile phone app to monitor their symptoms, and when information is reviewed weekly. We also expect that individuals with BP, in the study, will experience a decrease in manic and depressive symptoms, reinforcing the idea that monitoring symptoms can alone be therapeutic and can provide further impetus for individuals with BP to monitor their symptoms. Our study app was simple in its design: users can log, review, and visualize their mood. This simplicity ensures study results will generalize to the wealth of mobile and wearable technology developed for BP [15-20,22,23], translating into better technology for individuals with BP for monitoring symptoms.

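### The secondary analysis is worded as a test for an increase in YMRS and SIGHD although a decrease is hypothesised, and it reduces a numeric change to counts of rises and falls

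*Protocol article*

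**What the plan says.** The Secondary Outcome Measures section defines numeric outcomes, the first being "change from baseline in severity of manic symptoms, as measured with the YMRS"; the second is the same for depressive symptoms on the 17-item SIGHD. It states the expected direction: "We hypothesize that by tracking symptoms throughout the study, individuals with BP improve their symptoms". The Principal Findings part of the Discussion repeats it, expecting that participants "will experience a decrease in manic and depressive symptoms".

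The Statistical Tests section gives the rule: "we will test whether individuals experience a statistically significant increase in YMRS and SIGHD scores from baseline over the course of the 6-week study". The method it names, and what that method counts, is described in these words: "using McNemar test, which compares the number of individuals whose survey scores increased versus those whose survey scores decreased". The threshold for all tests is that "significance will be considered a *P* value less than .05". Whether tests are one- or two-sided is not stated.

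On scoring, the Log Your Mood section runs the app items from 0 (absent) to 3 (severe) and says the ordinal form was chosen "to be consistent with YMRS and SIGHD to clearly identify the absence of symptoms as zero". It also treats the YMRS and SIGHD totals as the reference for severity. A higher total is therefore a worse state.

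**The concern.** There are two separate problems in one sentence of the analysis section.

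1. **Direction.** The hypothesis is that scores fall; the test is worded for scores that rise. The article is the public pre-specification of this test, so the direction should not be left to interpretation once data are seen. Taken literally as a one-sided test, a significant result would mean worsening.
2. **Match of test to outcome.** The outcome is the amount of change on a total score, but the test uses only its sign. A 1-point change counts the same as a 15-point change, and an unchanged score carries no weight. The test does not by itself estimate the size of change.

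**Working it through.** The article gives no effect size, SD or power for the secondary outcomes, so there is no figure of its own to reproduce. The figures below are illustrations.

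**Inputs from the article.** 50 participants and about 10% to 20% attrition (Recruitment), so 50 × 0.90 = 45 to 50 × 0.80 = 40 completers; significance at P < .05 (Statistical Tests).

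**Assumptions.** Both arms are analysed together. The true standardised mean decrease is d = 0.3 to 0.5 SD. Changes are normal with no ties unless stated.

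**Step 1: direction, side by side.**

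| Section | Direction of scores |
|---|---|
| Secondary Outcome Measures | down (improvement) |
| Discussion, Principal Findings | down |
| Statistical Tests | up |

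**Step 2: one-sided test for an increase when the truth is a decrease.** The number of rises is Binomial(n, 1 − Φ(d)). The one-sided 5% critical count is the smallest r with P(X ≥ r | 0.5) ≤ 0.05.

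| n | r | P(significant), d = 0.3 | d = 0.4 | d = 0.5 |
|---|---|---|---|---|
| 40 | 26 | 0.00054 | 0.00008 | 0.00001 |
| 45 | 29 | 0.00033 | 0.00004 | 0.000004 |
| 50 | 32 | 0.00020 | 0.00002 | 0.000001 |

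All are below 0.001.

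**Step 3: two-sided reading.** McNemar's statistic on u rises and f falls is (u − f)² / (u + f). It is unchanged if u and f are swapped, so a fall is as detectable as a rise of the same size. This is the sign test. At n = 45 the exact two-sided test needs at least 30 changes in one direction (actual size 0.036).

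**Step 4: cost of using only the sign, normal changes.** Sign-test power is approximately P(X ≥ r) with X ~ Binomial(n, Φ(d)). Paired t power comes from the noncentral t with noncentrality d√n. Wilcoxon is by simulation.

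| n = 45, two-sided | d = 0.3 | d = 0.4 | d = 0.45 | d = 0.5 |
|---|---|---|---|---|
| Sign / McNemar | 0.31 | 0.51 | 0.61 | 0.70 |
| Paired t | 0.50 | 0.75 | 0.84 | 0.91 |
| Wilcoxon signed-rank | 0.49 | 0.73 | 0.82 | 0.90 |

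For d = 0.45: Φ(0.45) = 0.674 and P(X ≥ 30 | 45, 0.674) = 0.61. The asymptotic efficiency of the sign test relative to the t-test under normality is 2/π = 0.64, a loss of 1 − 0.64 = 0.36. If 20% of the 45 scores were unchanged (36 informative), sign-test power would be 0.22, 0.38 and 0.57 at d = 0.3, 0.4 and 0.5.

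**Step 5: the same comparison with heavy tails.** n = 45, mean decrease 0.45 SD, each distribution scaled to SD 1. P(fall) is 1 − 0.5·exp(−0.45√2) = 0.735 for Laplace, and the t₃ distribution function at 0.45√3 = 0.754 for t with 3 df. The sign test is calculated from these; the other two are simulated for the heavy-tailed cases (40,000 runs).

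| Distribution of changes | Sign | Paired t | Wilcoxon |
|---|---|---|---|
| Normal | 0.61 | 0.84 | 0.82 |
| Laplace | 0.89 | 0.83 | 0.91 |
| t, 3 df | 0.93 | 0.87 | 0.97 |

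The sign test loses heavily under normality and beats the t-test under heavy tails. Wilcoxon is above the sign test in all three.

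**The case against.** The strongest reply is that the article itself describes a symmetric comparison: the test "compares the number of individuals whose survey scores increased versus those whose survey scores decreased". No one-sided test is declared, and the other tests in that section are framed as tests of difference. On that reading a fall would be detected and the counts would show its direction. This stands. A reader might infer that the analysis cannot show improvement at all, but that holds only for a one-sided test, which the article does not specify. What remains is that the direction named is the opposite of the hypothesis and that nothing in the text settles the sidedness.

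The McNemar label is also defensible: on discordant counts it is a sign test, valid without distributional assumptions. The objection to it concerns efficiency and fit to the outcome, not validity. The loss against a t-test depends on the shape of the changes, as Step 5 shows.

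Two further inferences go too far:

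- *That the test discards most of the data.* Against a paired t-test on the same two visits, the loss under normality is about a third.
- *That only two of the seven assessments are used.* The comparison visit is not named. Day 42 against day 0 is the likely reading, but it is not stated, and a detailed protocol exists as an appendix that is not shown.

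Nor does the article rule out reporting a mean change alongside the test.

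**Conclusion.** The point holds in two parts. First, the direction in Statistical Tests contradicts the hypothesis and the expectation stated elsewhere in the same article. This rests on the text alone and needs correcting under either reading of sidedness. If the test is one-sided as worded, it cannot support the hypothesis; if two-sided, the fault is one of wording.

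Second, a numeric change-from-baseline outcome is tested by its sign only. The cost is about 23 percentage points of power against a paired t-test (84 − 61) and 21 against Wilcoxon (82 − 61), assuming 45 completers, a 0.45 SD change, normality and no ties. The comparison with the t-test can reverse under heavy tails. The gain from Wilcoxon persisted in the cases tried, though it falls to about 2 to 4 points there (91 − 89 and 97 − 93). Unchanged scores would reduce the sign test's power further. Only the secondary outcomes are affected; the primary outcomes are not.

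**What to change.** In Statistical Tests, replace *increase* with *change (two-sided; a decrease is hypothesised)* and name the comparison as baseline to day 42. Analyse the numeric change with a Wilcoxon signed-rank test, or with a mixed model on the weekly YMRS and SIGHD totals. Report the estimated change with a 95% CI, and keep the counts of rises and falls as description.

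This costs a couple of sentences and modest extra analysis work. The mixed model adds model assumptions. No new data are needed, because both scales are already scheduled at entry, at the five weekly interviews and at exit. The article reports only 3 people enrolled as of January 1, 2018, before participation began, so at that point the wording could have been corrected before outcome data were seen.
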